### Criteria for discontinuing or modifying allocated interventions {11b}

We have operationalized decision rules to identify any participant who is escalating in severity during the acute treatment phase that will be uniformly applied across treatment conditions. These subjects will be removed from the treatment protocol and referred for SAD treatment outside the study. First, any participant who demonstrates one of the serious adverse events described below (i.e., serious side effects to light therapy, mania or hypomania, or significant suicidal intent) will be removed from the treatment protocol. Second, participants who fall outside of the acceptable range for increasing SIGH-SAD scores (i.e., an increase of 12-points or more over pre-treatment SIGH-SAD score) for 2 consecutive or nonconsecutive weeks over the treatment phase will be removed from the treatment protocol. To operationalize this definition, we used prior data to generate the means and variability for the weekly SIGH-SAD scores for concurrent wait-list controls during the 6-week waiting phase when they were untreated [43]. The means and SDs were relatively consistent over the 6 weeks; therefore, we calculated the mean SIGH-SAD and its SD over the 6-weeks for the WLC condition (24.48 ± 5.78). Therefore, a 12-point increase over pre-treatment SIGH-SAD indicates a SIGH-SAD score that is 2 SDs above the typical variance observed for our wait-list controls. The reason that we specify 2 weeks is to minimize the chance that a temporary stressor contributed to a temporary exacerbation as opposed to a true treatment nonresponse. Even if removed from protocol, we will include all cases in the analysis and we will attempt to collect data from all participants, at each time point as the primary analysis is an intent-to-treat analysis of all randomized cases.

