Related to these two instances where we will remove a participant from the treatment protocol are cases where participants initiate outside treatment on their own during their study treatment. To assess the initiation of treatments outside of the study, we have added relevant questions to the beginning of each SIGH-SAD assessment. We will uniformly ask the question, “Have you started any new treatments outside of the treatment you are receiving in this study such as light therapy, talk therapy, or medications?” If a participant responds affirmatively, they will be queried by the interviewer for the details of this non-study treatment, which will be recorded. If a new treatment has been initiated, these cases will uniformly be considered as withdrawn from treatment protocol.

Study records include SIGH-SAD scores at each timepoint for each participant in the study. The project coordinator will monitor these records weekly to determine if any participant has met the criteria for protocol withdrawal. The PI will refer these cases for more intensive individual treatment from a local provider with training in treating SAD/depression. The project coordinator will also monitor weekly responses to the queries about initiating a new, non-study treatment to detect any treatment failures. Participants are informed that their progress over the study will be closely monitored; and, if at any time symptom severity escalates, the P.I. will discuss with them the possibility of referral for outside treatment.

To summarize, participants who experience a severe adverse event or meet our criteria for an excessive exacerbation in SIGH-SAD score during treatment will be removed from the treatment protocol and referred for outside treatment. Participants who decide to seek any outside treatment on their own will be coded as voluntarily withdrawn from protocol. According to intent-to-treat (ITT) principles, such participants will be encouraged to attend ongoing study monitoring (SIGH-SADs) to gauge their symptom severity and to participate in the follow-ups per the study assessment schedule. They will be included in ITT analysis as randomized, and also analyzed in an actual-treatment analysis. If initiation of outside treatment occurs, this event will be coded for in the database. Decisions about whether to consider this as a moderator of outcome, will be made in consultation with the Co-I study biostatistician (P.M.V.) based on how frequently this event occurs.

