### Sample size {14}

With a target *N* = 160 (80 subjects in each of the two treatments), the study will have 80% power to detect main effect differences of 22% (e.g., 28% vs. 50%) in winter 2 recurrence, which we expect at a naturalistic follow-up [14, 44]. Sample sizes for comparisons of winter 3 recurrence will depend on the number of recurrences at winter 2. Based on the recurrence rates observed in our prior study, we project that there will be about 37 recurrences in the LT group and 22 recurrences in the CBT-SAD group. This will provide 80% power to detect a difference in winter 3 recurrence of 35% (e.g., 60% vs. 25%) between CBT-SAD➔LT and LT➔CBT-SAD and a difference of 27% (e.g., 23% vs. 50%) between CBT-SAD and LT subjects without winter 2 recurrence. For biomarker comparisons, there will be 80% power to detect differences of 0.45 standard deviation (SD) in post-treatment values or in pre-post treatment changes between CBT-SAD and LT. Power for detecting relationships between biomarkers and outcomes were based on the odds ratio associated with an increase of 1 SD in the biomarker value or its change. For post-treatment remission, there will be 80% power to detect an OR of 2.2 in the CBT-SAD or LT group and a 2.4-fold difference in the ORs for the two treatments. For winter 2 recurrence, there will be 80% power to detect an OR of 2.2 in the LT group, an OR of 2.8 in the CBT-SAD group, and a 2.9-fold difference in their ORs. There was minimal attrition (4.5%) in our previous study, and we anticipate similar retention in this study. However, with attrition as high as 20%, there will be 80% power to detect a difference in winter 2 recurrence of 24% between CBT-SAD and LT and a difference of 39% in winter 3 recurrence between the two switch groups. Empirical sample size estimates^21^ indicate that the study will have at least 80% power to detect a mediated effect if the regression coefficient for the direct effect of treatment after adjustment for the mediator is at least .39 and the coefficients for the effect of treatment on the mediator and the effect of the mediator on outcome after adjustment for treatment are at least .26.

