## Statistical methods

### Statistical methods for primary and secondary outcomes {20a}

#### Data analysis

##### Aim 1

Logistic regression will be used to assess the effectiveness of treatment with either CBT-SAD or LT on depressive episode recurrence at winter 2. Covariates will be included in some analyses to assess the effect of treatment on outcomes after adjustment for any ongoing treatment reported at follow-up, such as any new treatment, psychotherapy, light therapy use in the CBT-SAD group, and antidepressant medication as in [name] et al. [14]. An intent-to-treat analysis will be conducted, using multiple imputation (MI) of missing next winter SIGH-SAD scores. Imputed scores will be used to classify depression recurrence status for individuals who dropped out or were lost to follow-up. Imputed values will be generated using the fully conditional specification (FCS) method to obtain regression estimates based on baseline and post-treatment SIGH-SAD (and component 21-item HAM-D and atypical subscale scores), demographic variables, comorbidity, and other baseline patient characteristics. Imputation will be done separately for the CBT-SAD and LT groups because data from our prior study indicate that the relationships between some of these variables and next winter recurrence differ in the two treatments. Ten data sets with imputed values will be generated and a dichotomous recurrence variable will be computed for each subject based on SIGH-SAD criteria. Logistic regression models will be fitted to each of the ten data sets and their parameter estimates will be combined using MI inference methods [43]. SAS PROC MI and PROC MIANALYZE will be used to carry out the imputation and analysis. The “missing at random” assumption of the MI analysis is valid if the imputation model is predictive of outcome. However, if we have an appreciable amount of missing data at follow-up, we will perform a sensitivity analysis using the pattern-mixture model approach (NMAR option in SAS 13.1) to assess the validity of the MI results.

Similar analyses will be performed to compare winter 3 outcomes in the CBT-SAD and LT subjects who did not have a winter 2 recurrence. Secondary analyses will examine the effects of treatment adherence within each treatment and the effect of therapist and therapy group within the CBT-SAD condition.

##### Aim 2

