### Methods in analysis to handle protocol non-adherence and any statistical methods to handle missing data {20c}

The data analysis is an intent-to-treat analysis with participants analyzed as randomized. Missing data will be handled through multiple-imputation as described in the analysis plan.

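### Aim 1 models adjusted for treatment reported at follow-up, with light use counted only in the CBT-SAD arm, do not estimate the randomised effect and can be biased towards either arm

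*Protocol article*

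**What the plan says.** Statistical methods {20a}, Aim 1, plans logistic regression of winter 2 recurrence on treatment. It adds: "Covariates will be included in some analyses to assess the effect of treatment on outcomes", specifically "after adjustment for any ongoing treatment reported at follow-up, such as any new treatment, psychotherapy, light therapy use in the CBT-SAD group", and antidepressant medication, following the prior trial's report. The list is illustrative. Light use is the only item restricted to one arm.

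The same section plans an intent-to-treat analysis "using multiple imputation (MI) of missing next winter SIGH-SAD scores". Section {11b} states that "the primary analysis is an intent-to-treat analysis of all randomized cases", and section {20c} that "The data analysis is an intent-to-treat analysis with participants analyzed as randomized". None of these places says which logistic model, adjusted or unadjusted, is the confirmatory one.

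Four other places bear on the point:
- The follow-up procedures record interim treatment use at the winter visits, alongside the SIGH-SAD.
- Provisions for post-trial care {30} describes September letters. Both arms are told to seek new treatment only where necessary, and LT participants are prompted to restart light at the first symptom.
- The LT description offers LT participants light boxes in winters 2 and 3.
- The choice of comparators {6b} reports that earlier differences between CBT-SAD and LT persisted after adjustment for re-treatment.

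**The concern.** Treatment taken up between post-treatment and winter 2 can be affected both by the arm and by the symptoms that define the outcome. Conditioning on it breaks the balance that randomisation gave.

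The light-use term does this in a particular way. It is zero for every LT participant by construction, so it takes CBT-SAD light users out of the arm contrast with no counterpart in LT. Symptom-triggered light use is adjusted out in one arm and kept as part of treatment in the other.

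What is at stake is how the adjusted result will be read. Section {6b} already uses persistence after adjustment for re-treatment as support for CBT-SAD. A similar adjusted result here is likely to be offered as evidence of robustness, which a model of this form cannot supply.

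**Working it through.** **1. The plan's own figure.** Inputs from Sample size {14}: "80 subjects in each of the two treatments" and "80% power to detect main effect differences of 22% (e.g., 28% vs. 50%) in winter 2 recurrence". Alpha is not stated, so two-sided 0.05 is assumed. For a Wald test of the log odds ratio:
- log OR = logit(0.28) − logit(0.50) = −0.944
- SE = √[1/(80×0.28×0.72) + 1/(80×0.50×0.50)] = 0.335
- power = Φ(0.944/0.335 − 1.96) = 80.6%

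The stated 80% reproduces. It supplies the arm size and rates used below and is not in dispute.

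**2. What the arm coefficient means.** Take logit P(recurrence) = β0 + β1·CBT + β2·(light use, CBT-SAD only). There are three cells and three parameters, so the fit is exact:

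β1 = logit(p0) − logit(p_LT), with p0 = (p_CBT − q·r)/(1 − q)

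Here p0 is recurrence among CBT-SAD non-users of light, q is the share of CBT-SAD using light, and r is recurrence among those users. Check with LT 40/80, CBT-SAD non-users 14/64 and users 8.4/16: ln(14/50) − ln(40/40) = −1.273, and a fitted logistic model also gave −1.273.

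**3. Direction and size.** The document gives neither q nor r, so both are assumed. With q = 20%:

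| p_CBT vs p_LT | r | p0 | Adjusted OR | Unadjusted OR |
|---|---|---|---|---|
| 28% vs 50% | 10% | 32.5% | 0.48 | 0.39 |
| 28% vs 50% | 28% | 28.0% | 0.39 | 0.39 |
| 28% vs 50% | 50% | 22.5% | 0.29 | 0.39 |
| 28% vs 50% | 70% | 17.5% | 0.21 | 0.39 |
| 45.6% vs 45.6% | 20% | 52.0% | 1.29 | 1.00 |
| 45.6% vs 45.6% | 45.6% | 45.6% | 1.00 | 1.00 |
| 45.6% vs 45.6% | 70% | 39.5% | 0.78 | 1.00 |

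One row in full: (0.456 − 0.20×0.70)/0.80 = 0.395; the odds are 0.653 against 0.838, so OR = 0.78.

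With equal arms, r = 70% gives a 10.9% chance of a false finding for CBT-SAD, and r = 20% an 11.5% chance of one for LT; nominal is 2.5% per side. With q = 10% at 28% vs 50%, the OR runs from 0.43 (r = 10%) to 0.30 (r = 70%). The coefficient moves towards CBT-SAD only if light users recur more often than the CBT-SAD average.

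**4. Simulation with symptom-driven uptake.** Assumptions: 80 per arm; 40% recurrence in both arms; log odds of recurrence rising 1.5 per SD of early-winter symptoms; 20% of CBT-SAD using light. The model contains arm and light use only.
- Light without effect: median OR 0.81 and two-sided type I error 8% when the log odds of uptake rise 1 per SD of symptoms; 0.77 and 12% at 1.5 per SD; 0.73 and about 14% at 2 per SD.
- Light protective, log OR −1: OR 0.96, 0.90 and 0.85 at the same three slopes.
- Light strongly protective, log OR −2: OR 1.11, 1.04 and 1.02.
- Other uptake, light without effect: about 0.84 to 0.92 and 5 to 8% at 10% uptake; about 0.62 to 0.76 and 12 to 25% at 30%.
- LT participants taking up other treatment equally (20%, same symptom dependence), adjusted for by its own indicator: OR about 0.98 to 1.00, type I error about 5%.

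The unadjusted model held 3 to 6% in data generated this way.

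**The case against.** The strongest reply is that nothing primary is touched. The covariates enter only some analyses, and sections {11b} and {20c} make the main analysis intent-to-treat. That stands. A reader might infer that the confirmatory result is compromised, and the document does not support this. What remains is that analysing participants as randomised does not by itself mean without post-randomisation covariates, and the article does not name the confirmatory model.

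A reader might also infer that the bias favours CBT-SAD, because worsening participants would be the ones who turn to light. The letters make symptom-driven uptake plausible, but recurrence among users is not given, and the protocol itself regards light as efficacious. The working shows movement either way, although reversal needs a strong light effect.

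The restriction to CBT-SAD also has a reason: in LT, light is the allocated treatment and its use is adherence. Worsening LT participants who add psychotherapy, medication or another new treatment are adjusted for too, so the two-term simulation is not the full planned model. Both points stand. They explain the asymmetry and may shrink the bias, but the conditioning on post-randomisation treatment remains.

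Two side issues carry little weight. Section {11b} leaves open "Decisions about whether to consider this as a moderator of outcome", but this concerns outside treatment started during study treatment, not re-treatment before winter 2. Only SIGH-SAD scores are described as imputed, so adjusted models may lose people without follow-up treatment data. The article does not say that they will, and the anticipated 4.5% attrition is about 7 of 160.

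**Conclusion.** The concern holds in a limited form. The treatment-use-adjusted Aim 1 models condition on variables that arise after randomisation and are measured with the outcome, so their arm coefficient does not estimate the randomised effect. With the light-use indicator alone, that coefficient contrasts a selected part of the CBT-SAD arm with the whole LT arm; this is algebra and needs no assumption.

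The size and direction do rest on assumptions. In the two-term model with equal arms and 20% uptake, the simulated OR runs from about 0.75 to 1.1, with type I error about 8 to 12% when light has no effect and about 14% at the steepest symptom dependence. Setting recurrence among users directly gives 0.78 to 1.29 for rates of 70% down to 20%. If LT participants take up other adjusted-for treatment equally, the bias nearly disappears. Neither a bias towards CBT-SAD nor any effect on the intent-to-treat primary analysis is established.

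**What to change.** - Name the intent-to-treat contrast in the imputed data sets as the sole confirmatory Aim 1 test, either unadjusted or adjusted only for baseline variables such as the stratification factors.
- Drop the one-arm light-use covariate from any model offered as an estimate of the treatment effect.
- Tabulate interim treatment use by arm.
- Label any model that still conditions on treatment reported at follow-up as descriptive, and do not present it as confirmation that the effect withstands re-treatment.
- If an analysis counting new treatment as failure is added, label it as a different question from SIGH-SAD recurrence. State its asymmetry: light use would count as failure in CBT-SAD but is allocated treatment in LT.

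The cost is wording, plus less direct comparability with the prior trial's adjusted models. No data collection changes.

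### Ten imputations, fixed whatever the missing fraction, leave small but avoidable seed noise in the primary winter 2 p-value; 100 or more would cut most of it at almost no cost

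*Protocol article*

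**What the plan says.** Under Statistical methods {20a}, Aim 1, missing winter 2 SIGH-SAD scores are multiply imputed, and "Imputed scores will be used to classify depression recurrence status for individuals who dropped out or were lost to follow-up". On the arms: "Imputation will be done separately for the CBT-SAD and LT groups". On the number of imputations: "Ten data sets with imputed values will be generated and a dichotomous recurrence variable will be computed for each subject". On pooling: "Logistic regression models will be fitted to each of the ten data sets and their parameter estimates will be combined using MI inference methods".

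The winter 3 comparison in participants without a winter 2 recurrence (Aim 1) and the switch comparison (Aim 3) are described as similar to this analysis. Ten is not restated there, but it appears to carry over.

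Sample size {14} gives two attrition levels. The expected one: "There was minimal attrition (4.5%) in our previous study, and we anticipate similar retention in this study". The pessimistic one: "with attrition as high as 20%, there will be 80% power to detect a difference in winter 2 recurrence of 24" percentage points. Nothing links the number of imputations to the amount that turns out to be missing.

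**The concern.** A participant whose winter 2 score is missing receives an imputed score, which is then cut into recurrence or no recurrence. That status can change from one imputed data set to the next. Averaging over ten data sets leaves some of this variation in the pooled log odds ratio, so the same trial data analysed with another random seed give a slightly different p-value.

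For most results this does not matter. For a result near the significance threshold, the superiority conclusion could differ between two equally correct runs of the same plan. The noise grows with the fraction of missing data, yet the plan holds the number of imputations at ten throughout.

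**Working it through.** **Inputs from the protocol article**
- Number of imputations, m = 10 (Aim 1).
- 80 per arm; power statement of 28% vs 50% (Sample size {14}).
- Projected recurrences: 37 LT and 22 CBT-SAD (Sample size {14}).
- Attrition 4.5% (160 × 0.045 ≈ 7 people) or 20% (160 × 0.20 = 32 people).

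**Assumptions not in the document**
- Two-sided α = 0.05.
- Fraction of missing information (FMI) about equal to the missing fraction.
- Normal approximation for the pooled test.

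**1. The plan's own power figure.** Wald test of the log odds ratio, 80 per arm:
- Log OR = ln(0.50/0.50) − ln(0.28/0.72) = 0.944.
- SE = √(1/(80×0.50×0.50) + 1/(80×0.28×0.72)) = 0.335, so z = 2.82.
- Power = Φ(2.82 − 1.96) = 80.6%.

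The stated 80% is reproduced. With 64 per arm and a 24-point difference, a pooled two-proportion test gives 79.9%, so the 20% attrition figure is reproduced too.

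**2. Expected z at the projected counts.**
- Log OR = ln(37/43) − ln(22/58) = 0.819.
- SE = √(1/37 + 1/43 + 1/22 + 1/58) = 0.336.
- z = 2.44, p = 0.015, power about 68%.
- At 20% attrition, z = 2.44 × √0.8 = 2.18.

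**3. Efficiency with ten.** 1/(1 + FMI/m) = 1/(1 + 0.0045) = 99.6% at 4.5%, and 1/(1 + 0.02) = 98.0% at 20%.

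**4. Seed noise.** The SD of the pooled z over seeds is about √(FMI/m), or √(FMI/(m+1)) if FMI is defined relative to the finite-m variance.
- m = 10: 0.064–0.067 at 4.5%; 0.135–0.141 at 20%.
- m = 100: 0.021 at 4.5%; 0.044–0.045 at 20%.

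**5. What this does to p.** Suppose the p-value with unlimited imputations (the limiting p) were 0.05. The central 95% of runs, using the m+1 form, would give:

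| Missing | m = 10 | m = 100 |
|---|---|---|
| 4.5% | 0.037–0.067 | 0.045–0.055 |
| 20% | 0.026–0.090 | 0.041–0.061 |

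For a limiting p of 0.04 (z = 2.054), the chance that one ten-imputation run lands above 0.05 is Φ(−0.094/0.067) = 8% at 4.5% missing and Φ(−0.094/0.141) = 25% at 20%.

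**6. How often two runs disagree.** For a given limiting z, the chance is 2q(1 − q), with q = Φ((z − 1.96)/s) and s the SD from step 4. Averaging over z ~ N(μ, 1):
- Projected rates: μ = 2.44 at 4.5% missing and 2.18 at 20%.
- Powered-for difference: μ = 2.82 at 4.5% missing and 2.82 × √0.8 = 2.52 at 20%.

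| | m = 10 | m = 100 |
|---|---|---|
| All trials, 4.5% missing | 2–3% | about 1% |
| All trials, 20% missing | 5–6% | about 2% |
| Trials with p 0.03–0.08, 4.5% missing | about 18% | about 6% |
| Trials with p 0.03–0.08, 20% missing | about 34% | about 12% |

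Under the projected rates, about 15–16% of trials fall in that p-value window.

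**7. Check by simulation.** This used arm-separate imputation of a continuous score, dichotomised and pooled by Rubin's rules, with assumed predictor correlations of 0.3 or 0.5. At 20% missing and m = 10, the seed SD was 0.126–0.133 of the SE and overall disagreement was 6–7%. At 4.5% missing, disagreement was 2–3%. Both agree with the formula.

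**The case against.** The strongest reply is that nothing in the plan is wrong. Rubin's pooled variance includes the (1 + 1/m) term, so ten imputations give valid inference at almost full efficiency. A reader might infer a biased test or an inflated type I error; the plan as written does not support that. This part of the reply stands, and it makes the point an improvement rather than a correction.

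A reader might also infer that most of the primary test is imputed. It is not. At the anticipated 4.5% attrition, about 153 of 160 outcomes are observed and identical in all ten data sets.

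The 18% and 34% rates should not be read as the chance that this trial's conclusion flips. They apply only to the minority of trials that land near 0.05. At 4.5% missing, a limiting p of 0.03 or below, or of 0.08 or above, practically never flips (about 0.1%).

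The 20% level is a power check and not the expectation. The article commits to following dropouts, and when the pandemic halted in-lab biomarker work, SIGH-SAD interviews moved to videoconference. The pandemic passage therefore does not show that primary outcomes were lost. The planned pattern-mixture analysis for appreciable missing data addresses the missing-at-random assumption, not Monte Carlo noise, so it does not answer this point.

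Finally, no finite number of imputations removes seed dependence. That is true, but it does not argue for keeping ten when a larger number is nearly free. The absence of a seed or of a Monte Carlo error report from the article is no defect, since such details usually sit in the analysis plan.

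**Conclusion.** The point holds as a minor improvement. The number of imputations is stated rather than left open, and it is lower than a confirmatory comparison needs for a stable p-value if missing data approach 20%. At the attrition the trial expects, the practical effect is small, roughly one trial in 40. At 20% it is roughly one in 17. In both cases it is concentrated in results close to 0.05.

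The size rests on the two-sided 0.05 level, on FMI being close to the missing fraction, and on the projected or powered-for recurrence rates. Good imputation predictors would lower FMI and the noise with it: the simulations gave FMI of about 0.16–0.18 at 20% missing.

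**What to change.** In Aim 1, replace ten by at least 100 imputed data sets, and apply the same number to the winter 3 comparison and the switch comparison where they use this method. The imputation model, the separate imputation by arm, the classification rule and the pooling stay as they are.

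The cost is one number in the plan and a short increase in SAS run time. There is no statistical downside.
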